### **Randomization and Blinding**

- **Randomization:** Patients will be allocated with 1:1 ration into treatment (real IFC) or control (sham IFC) groups using computer-generated block randomization (block size = 4).
- **Blinding:**
  - **Patients:** Sham IFC will be applied for 1 minute (at perceptible but non-therapeutic intensity) to mimic active treatment. Real IFC will be applied with the strong tolerable intensity.
  - **Outcome assessor (urologist):** Blinded to group assignment.
  - **Therapist:** Unblinded due to treatment nature.
- **Allocation concealment:** Sealed opaque envelopes (prepared by an independent person) will ensure concealment until intervention begins.

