## **Summary of Methodology and Analysis**

### **Study Design**

Following ethical approval, a non-probability convenience sampling method will be employed. A urologist will evaluate patients with voiding dysfunction through:

- **Clinical history** (symptom assessment)
- **Neurological examination** (anal tone, voluntary anal control, genital/limb reflexes, sensory evaluation)
- **Urodynamic tests** (cystometry for detrusor pressure, uroflowmetry and pre-/post-void ultrasound to classify voiding dysfunction)

Eligible patients will complete a 3-day voiding diary (recording fluid intake, voiding frequency, and urinary patterns). They will then be referred to the physiotherapy clinic of rehabilitation faculty of Iran university of medical science with all of medical records. The urologist will remain blinded to group allocation. At the physiotherapy clinic, all participants will first receive a comprehensive explanation of the entire procedure and the purpose of the study. Then, individual informed consent forms will be obtained from each participant. Patients will be informed that there are two treatment groups, and except for the method of applying the interferential electrical current, all treatments in both groups are similar. Group assignment will be completely random, with an equal chance of being placed in either group. They will also be assured that if significant improvements are observed at the end of the study, the treatment received by the other group will be fully provided to them.

A completed 3-day urinary diary will be collected from each patient, and from this data, the frequency of bathroom visits within 24 hours will be extracted. Using a computerized random number list, patients will then be randomly assigned to either the treatment or control group in a 1:1 ratio, using blocks of four.

Next, a self-developed questionnaire collecting personal information such as age, height, and weight will be completed by all patients in both groups at the beginning of the first session. Afterward, all patients will receive the Persian versions of the female lower urinary tract symptom (FLUTS-ICIQ) and pelvic floor distress inventory-20 (PFDI-20) questionnaires to score the severity of their lower urinary tract symptoms and pelvic floor symptoms, respectively.

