## 2. Randomization and Blinding

- **Randomization:**
  - Computer-generated block randomization (1:1 ratio, block size=4).
  - Stratified by age and symptom severity.
- **Blinding:**
  - **Patients:** Sham-controlled (details below).
  - **Outcome Assessor (Urologist):** Blinded to group allocation.
  - **Therapist:** Unblinded due to intervention nature.

Presenters and colleagues

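### One fixed block size of 4, at one clinic with an unblinded therapist, could let up to a third of assignments be deduced, so envelopes alone do not secure concealment

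*Protocol*

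**What the plan says.** The block size is fixed in three places. Randomization and Blinding (in the methodology summary) gives "computer-generated block randomization (block size = 4"). Study Design says women are assigned "in a 1:1 ratio, using blocks of four". The later numbered section, 2. Randomization and Blinding, has "Computer-generated block randomization (1:1 ratio, block size=4") and adds "Stratified by age and symptom severity". The other two places do not mention stratification, and no cut-points or number of strata are given.

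On location, Study Design says of eligible patients: "They will then be referred to the physiotherapy clinic of rehabilitation faculty of Iran university of medical science". The explanation of the study follows at that clinic, and then "individual informed consent forms will be obtained from each participant". Diary collection and random assignment come next.

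On who knows what, the therapist is "Unblinded due to treatment nature". The urologist, who evaluates patients before referral and assesses outcomes, is blinded. An independent person prepares sealed opaque envelopes, and the Protocol claims that these guarantee concealment up to the start of the intervention.

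The Protocol does not say who takes consent, who sets the order of entry, who opens the envelopes, whether one therapist treats everyone, or whether the block size is kept from clinic staff.

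**The concern.** Opaque envelopes protect against reading the next allocation. They do not protect against inferring it. With a constant block of 4 at 1:1, each block holds two real and two sham assignments. Once three are known the fourth is fixed, and if the first two are the same, the third and fourth are both fixed. The person who delivers real or sham current learns each treated woman's arm, and the block size stands in the Protocol.

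If someone with that knowledge could affect whether or when the next woman is consented or entered, the arms could differ at baseline for reasons other than chance. This would bear on every primary measure (Qmax, voiding time, PVR and ICIQ-FLUTS), not only the self-reported one, because it acts on who enters each arm and not on how the outcome is read. A blinded assessor does not correct it.

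The planned analysis gives limited protection. Statistical Analysis compares the arms at each time point by t-test or Mann-Whitney without baseline adjustment. The repeated-measures ANOVA includes baseline only as one of the time points. With 14 per arm, a few selectively timed entries could move a mean.

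**Working it through.** The Protocol gives no figure for predictability, so there is none to reproduce. Inputs: block size 4 and ratio 1:1 (Study Design and both randomisation sections); 14 per group, so N = 28 (Sample Size Calculation Method). The observer is assumed to know the block size and all earlier assignments.

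**Certain assignments, one unstratified list.** A block of two A and two B has 6 equally likely orders: AABB, ABAB, ABBA, BAAB, BABA, BBAA.

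- Positions 1 and 2 are never certain.
- Position 3 is certain only if the first two are equal (AABB, BBAA): 2/6 = 1/3.
- Position 4 is always certain: 1.
- Expected number per block: 0 + 0 + 1/3 + 1 = 4/3. Share: (4/3)/4 = 33.3%.
- N = 28 is 7 full blocks: 7 × 4/3 = 9.3 assignments.
- The budget lists 300 stimulation sessions. At 10 per woman that implies 30 women. The two extra women take positions 1 and 2 of an eighth block and add nothing: 9.3/30 = 31.1%.

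**Best-guess accuracy, same list.** The observer always guesses the arm with more places left in the block.

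- Position 1: 1/2.
- Position 2: 2/3.
- Position 3: (1/3 × 1) + (2/3 × 1/2) = 2/3.
- Position 4: 1.
- Average: (0.500 + 0.667 + 0.667 + 1.000)/4 = 70.8%, against 50% for an observer with no information.

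**If stratification applies.** Each stratum has its own blocks, and many end incomplete. A stratum with c women has floor(c/4) × 4/3 expected certain assignments, plus 1/3 if three women are left over. The number of strata is not given, so the table assumes K equally likely strata (simulation, N = 28).

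| Strata K | Expected certain | Share |
|---|---|---|
| 1 | 9.3 | 33.3% |
| 2 | 8.5 | 30.3% |
| 4 | 7.7 | 27.4% |
| 6 | 6.8 | 24.4% |
| 9 | 5.4 | 19.4% |

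The observer would also have to track each stratum separately.

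**Effect of varying the block size.** Simulation, unstratified, N = 28. The observer knows the set of sizes but not their order, and updates after each allocation.

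| Block sizes | Certain | Best guess correct |
|---|---|---|
| 4 only | 33.3% | 70.8% |
| 4 and 6 | 5.8% | 68.7% |
| 4, 6 and 8 | 2.2% | 67.5% |

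Mixing sizes removes most of the certainty (from 9.3 to about 0.058 × 28 = 1.6 assignments) but little of the better-than-chance guessing.

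**The case against.** The strongest reply is that permuted blocks with sealed opaque envelopes prepared by an independent person are a recognised concealment method, and that no route to bias has been shown. Much of this stands. A blinded urologist evaluates the women before they reach the clinic. Consent precedes assignment. Nothing says that the unblinded therapist takes consent, books patients, opens envelopes or treats every woman. The Protocol also calls the principal investigator a physiotherapist, and a reader might infer that this is the treating therapist. The documents do not say so.

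Three stronger readings are tempting and not supported:

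- A reader might infer that a third of assignments are known in advance. One third is an expected share, for an observer with full history and an unstratified list. It is lower if the stratification applies.
- A reader might infer that concealment has failed or that the therapist chooses whom to enter. The documents leave those roles open. The percentages measure predictability, and the size of any resulting bias is not estimated.
- A reader might infer that the risk is serious because the primary outcomes are self-reported. 4. Outcome Measures lists Qmax, voiding time and ultrasound PVR beside ICIQ-FLUTS, and the urologist who measures PVR and records Qmax is blinded.

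What the reply does not remove is that assessment before referral leaves consent and order of entry at the clinic. No provision keeps the block size, the consent step or the envelopes away from someone who knows past allocations.

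**Conclusion.** The point holds as a design weakness. Fixing a single block size of 4 at one clinic with an unblinded therapist means that envelopes alone do not deliver the concealment the Protocol claims. An observer who knows the block size and all earlier allocations could deduce up to a third of assignments: 33%, about 9 of 28, if unstratified, or about 19% to 30% with 2 to 9 strata. That range rests on an assumption of equal strata. Whether such an observer has any influence on entry is not stated either way, so the risk is possible and not demonstrated. Separately, the Protocol contradicts itself by omission: one section stratifies and the other two do not. A cheap improvement is warranted, and it should be made before enrolment.

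**What to change.** 1. In Study Design and in both randomisation sections, replace the fixed block size with randomly varying block sizes (for example 4 and 6), generated by the independent person who prepares the envelopes and not disclosed to the clinic.
2. State by role that existing staff other than the treating therapist take consent, and that they open the next envelope only after consent and baseline data are recorded. Study Design currently describes the baseline questionnaires after assignment, so that order would need to change. This step is needed because varying the block size leaves best-guess accuracy at about 69%.
3. Make the three sections agree on stratification. If it is kept, each stratum needs its own list.

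The cost is one regenerated list before enrolment (or one per stratum), edits to three sections, and a second staff member at entry. If enrolment stops inside a block of 6, the arms can differ by up to 3, against up to 2 with blocks of 4. With stratification, this can occur in each stratum, which is noticeable among 28 women.

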### **Statistical Analysis**

Descriptive information regarding the demographic characteristics of individuals in both groups will be given as means (standard deviations) for quantitative variables and as frequencies (percentages) for qualitative variables. For comparing of each demographic variable between the two study groups, the independent t-test for normally distributed quantitative variables and the Mann-Whitney test for non-normally distributed quantitative variables will be applied. The chi-square test will be conducted to compare qualitative variables.

The normality of the data in the study groups will be tested using the Shapiro-Wilk test. To comprehensively examine the extracted data, the following procedures will be carried out, as elaborated below.

To compare the mean of each variable in both groups before the intervention, two weeks after the intervention, and after a three-month follow-up period, the two-way repeated measures ANOVA will be employed, assuming the data are normally distributed. In the case of non-normality, a nonparametric equivalent will be used.

For the comparison of the mean of the variables between both groups at every time point (before the intervention, at two weeks after the intervention, and after a three-month follow-up), the two independent sample t-test will be used if the data is normally distributed and the Mann-Whitney test if the data is distributed non-normally.

To determine differences in the mean of the variables of both groups over the study period, the one-way repeated measures ANOVA will be used. In the presence of a statistically significant difference in the variable mean over time, the post hoc test with Bonferroni and Tukey corrections will be utilized. The data will be analyzed using SPSS version 26 software. The significance level in this study is assumed to be 5%.

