### 1. PVR:

- $H_0$ : There is no significant difference in mean PVR before and after treatment in the real IFC group.
- $H_0$ : There is no significant difference in mean PVR after treatment between the real IFC and sham IFC groups.

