#### **Outcomes:**

- **IFC group showed:**
  - Significant reduction in PVR ( $p<0.05$ )
  - Increased voiding frequency ( $p<0.05$ )
  - Improved Qmax and reduced voiding time ( $p<0.05$ )
  - 77% normalized urinary flow pattern vs. 33% in urotherapy-only group.

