### **Protocol Deviations Management**

- **Non-Adherence:** Participants missing >2 sessions excluded from per-protocol analysis.
- **Adverse Events:** Documented and reported to ethics board (e.g., skin irritation from electrodes).

This protocol aligns with CONSORT guidelines for non-pharmacological trials. Let me know if you need additional operational details!

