#### **Sample Size Calculation Method**

Based on the study by Kajbafzadeh et al. and considering a 95% confidence level and 80% test power, the sample size was calculated as 14 participants per group (20).

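### The between-group tests leave out the baseline already collected, and the repeated-measures ANOVA drops any woman with a missed visit; one baseline-adjusted mixed model would repair both

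*Protocol*

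**What the plan says.** The Statistical Analysis section names two routes to a between-group result.

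- By visit: "For the comparison of the mean of the variables between both groups at every time point" (baseline, two weeks after the intervention, three months), a two-sample t-test or, if the data look non-normal, a Mann-Whitney test. No baseline term is mentioned.
- Over time: for the same three time points, "the two-way repeated measures ANOVA will be employed, assuming the data are normally distributed". Otherwise, "In the case of non-normality, a nonparametric equivalent will be used". A Shapiro-Wilk test on the trial data decides which.

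The between-group hypotheses under Research Questions & Hypotheses concern values after treatment. For PVR: "There is no significant difference in mean PVR after treatment between the real IFC and sham IFC groups". Qmax, 24-hour frequency, ICIQ-FLUTS and PFDI-20 follow the same pattern. All five have a pre-treatment value under Study Design and Assessment Timeline.

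Both limitations sections name attrition over follow-up as the risk. The only analysis-set rule is under Protocol Deviations Management: "Participants missing >2 sessions excluded from per-protocol analysis". The second randomisation section lists age and symptom severity as stratification factors; neither appears in the analysis.

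**The concern.** With 28 patients, the baseline value is the cheapest source of precision, and the tests that answer the stated hypotheses leave it out.

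The ANOVA uses baseline only indirectly, as a time level. The protocol does not say whether its group effect, its interaction or the by-visit tests decides the question. In its classical form it also excludes anyone without all three visits, so a woman who misses only the three-month visit loses her two-week result too.

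The Shapiro-Wilk step leaves it to the data whether means or ranks are compared, so the effect measure is not fixed in advance for an endpoint such as PVR, which may well be skewed.

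The protocol itself fixes these methods, so the point does not depend on the unseen analysis plan.

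**Working it through.** **Inputs from the protocol.** "The significance level in this study is assumed to be 5" per cent (two-sided assumed). Size: "considering a 95% confidence level and 80% test power, the sample size was calculated as 14 participants per group". Allocation 1:1. No endpoint, difference, SD, baseline-outcome correlation or dropout rate is given.

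**The protocol's own figure.** Fourteen per group cannot be reproduced from what is stated. The only between-group numbers reported from the cited paediatric study are binary: "77% normalized urinary flow pattern vs. 33% in urotherapy-only group". The two-sided unpooled formula gives (1.960 + 0.842)² × (0.77×0.23 + 0.33×0.67) / 0.44² = 7.85 × 0.398 / 0.194 = 16.1, so 17 per group. The pooled form gives 19. One-sided versions give 13 (unpooled) and 15 (pooled), but nothing says that this outcome or a one-sided test was used.

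**Effect implied by 14 per group.** For a continuous endpoint, d = (1.960 + 0.842) × √(2/14) = 1.06 SD by the normal approximation, or 1.10 SD by the t distribution. I use 1.10. This effect is back-solved and does not appear in the protocol.

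**Unadjusted t-test.** Noncentrality 1.10/√(2/14) = 2.91 on 26 df gives 80% power.

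**Baseline-adjusted ANCOVA.** Residual variance is multiplied by (1 − r²), so noncentrality becomes 2.91/√(1 − r²) on 25 df. This gives 83.4%, 89.8%, 93.8% and 97.5% for r = 0.3, 0.5, 0.6 and 0.7. The formula ignores the small cost of chance baseline gaps; simulation includes it and gives the lower figures below.

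**Simulation.** 14 per group, normal data, equal correlation r among the three visits, and an effect of 1.10 SD at both post-treatment visits:

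| r (assumed) | Unadjusted t-test, one visit | ANCOVA, one visit | ANOVA group-by-time |
|---|---|---|---|
| 0.3 | 80% | 82% | 70% |
| 0.5 | 80% | 88% | 84% |
| 0.6 | 80% | 93% | 92% |
| 0.7 | 80% | 97% | 97% |

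For equal precision, ANCOVA needs about 14 × (1 − r²) per group: 12.7, 10.5, 9.0 and 7.1.

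**Missing visits.** If 12 of 14 per group have all three visits (14% lost, assumed), group-by-time power at r = 0.5 falls from about 84% to 77%. If 10%, 20% or 30% of values are missing at the visit tested, the unadjusted t-test falls from 80% to about 75%, 70% or 63%.

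**Normality switch.** In 20,000 simulated trials at 14 per group, the two-stage procedure kept type I error at 5.1% for normal data, and at 5.2% and 4.7% for lognormal data (sigma 0.5 and 0.8). Mann-Whitney was selected in 9.6% of the normal trials and in 59% and 88% of the lognormal ones.

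**The case against.** The strongest reply is that the planned ANOVA already uses baseline. A reader might look at its group main effect, which averages in a visit with no treatment difference and has only 63%, 58% and 55% power at r = 0.5, 0.6 and 0.7, and conclude that the plan is badly underpowered. That is the wrong term. In this layout group-by-time carries the treatment effect, and at r of 0.6 or more it is within about a point of ANCOVA. What remains is that it is an omnibus test over three visits, gives no adjusted difference with an interval at a stated visit, needs complete visits, and does clearly worse at r = 0.3.

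Three other strong readings also fail.

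- That no nonparametric equivalent exists: the protocol names none, and rank-based methods for group-by-time designs are available. The fallback is unnamed, not impossible.
- That Shapiro-Wilk picks the method more or less by chance, or inflates error: the simulation shows that it follows the data's shape and keeps type I error near 5%. The harm is an effect measure left open.
- That only per-protocol patients will be analysed: a rule about exclusion from a per-protocol analysis suggests that another set exists. PGI-C is similar. It has no baseline and cannot enter the three-visit ANOVA, but its only hypothesis is between groups after treatment, which the planned two-sample tests cover.

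It is also true that unadjusted tests are valid under randomisation: chance baseline imbalance is already within the 5% error, and stratifying by symptom severity would reduce it. The case for change is precision and a fixed estimand, not validity.

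**Conclusion.** The concern holds as a should-fix. The tests that match the stated hypotheses ignore baseline and give up about 2 to 17 points of power (80% against 82% to 97%) over r = 0.3 to 0.7. The ANOVA recovers most of this when r is 0.6 or more, but it loses patients with one missed visit (about 84% to 77% at r = 0.5 with 12 per group) and does not deliver the contrast that the hypotheses ask for.

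The sizes rest on a back-solved effect of 1.10 SD, assumed correlations and loss, equal correlation between visits, and normal data. The direction for ANCOVA against the unadjusted test was the same at every correlation tried. Exclusion of incomplete patients is inferred from the classical method named; the protocol does not state it. The protocol does not support reading the planned tests as invalid.

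**What to change.** For endpoints with a baseline, make the primary between-group analysis one prespecified mixed model (SPSS MIXED) on the post-baseline visits. Include group, visit, group-by-visit, the baseline value and the stratification factors listed in the second randomisation section. Include all randomised patients with any post-baseline value, analysed as assigned, and report the adjusted group difference with its 95% confidence interval at a prespecified visit.

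Decide the handling of skewed PVR now, for example by a log transformation that allows for zeros, and remove the Shapiro-Wilk choice between means and ranks. Analyse PGI-C separately at its own visit. Keep the per-protocol analysis as a sensitivity analysis.

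Cost: mainly rewording, with the same data and software. The model spends a few degrees of freedom and adds a modelling assumption. Naming the visit also means reconciling the post-treatment timing, which Statistical Analysis puts two weeks after the intervention and Assessment Timeline puts after the ten sessions.

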## Ethical Considerations

### **Ethical Concerns and Issues in the Study:**

1. Group allocation and differential treatments may lead to variations in treatment outcomes.

### **Solutions to Ethical Issues:**

1. Prior to intervention, all patients will receive a full explanation of group allocation and treatments. All patients will be assured that if any clinically significant improvement is demonstrated in either group, the effective treatment will be provided to the other group with the same duration and quality after study completion.
2. Participation is entirely voluntary. Written informed consent will be obtained from all patients before treatment initiation.
3. Principles of confidentiality and data protection will be strictly maintained.
4. All participants retain the right to withdraw from the study at any stage without consequences.

